### Outcome measures

Outcome measures are divided into primary and secondary outcomes. These measures will be obtained from both intervention and control groups at baseline and 6 months after the delivery of the intervention.

### Primary outcome

The primary outcome will be measured by the mean change in patient activation score using the Patient Activation Measure short form–Malay version (PAM-13-M) questionnaire [24].

### Secondary outcomes

Change in mean WCChange in mean BMIChange in mean systolic and mean diastolic BPChange in PA level will be measured by the International Physical Activity Questionnaire short form–Malay version (IPAQ-M) [70].Change in eating behaviour will be measured by the Dutch Eating Behaviour Questionnaire–Malay version (DEBQ-M) [71].Change in patients’ perceptions and experiences of receiving care for chronic conditions will be measured by the Patient Assessment of Chronic Illness Care–Malay version (PACIC-M) questionnaire [72].Change in patient–physician satisfaction will be measured by the Skala Kepuasan Interaksi Perubatan (SKIP-11) questionnaire [73].Change in accuracy of CVD risk perception will be measured by the absolute difference between the perceived absolute 10-year CV risk and the actual calculated risk by Framingham Risk Score (FRS) general CVD risk prediction chart [74–76].

### Control group

The control group will continue to receive usual care at the university primary care clinic. They will be given the EMPOWER-SUSTAIN Global CV Risks Self-Management Booklet, as this is considered as usual care at the university primary care clinic. The EMPOWER-SUSTAIN self-management mobile app will be made available to the control group at the end of the study. During the course of the study, there will be no limit to the number of clinic visits that a patient is allowed to make in either the intervention or control group. Figure 4 shows the EMPOWER-SUSTAIN schedule of enrolment, interventions and assessments according to SPIRIT guidelines [40].

**Fig. 4 Fig4:**
[figure not shown]
The EMPOWER-SUSTAIN Standard Protocol Items: Recommendations for Interventional Trials (SPIRIT) schedule of enrolment, intervention and assessment

### Study procedures

All interviewers and investigators will be trained regarding the study procedures prior to the conduct of the study to minimise variability in the method of data collection. Data will be collected at baseline and 6 months after delivery of the intervention. The study procedures will be conducted in accordance with the Malaysian Guideline for Good Clinical Practice, Fourth Edition, 2018 [77].

### Demographic and anthropometric data collection

A standardised case report form (CRF) will be used to collect socio-demographic information of the patients (age, sex, ethnicity, patient contact details, educational attainment, and occupation), smoking status (including the number of cigarettes smoked per day for current smokers) and other clinical information (presence of comorbidities, past medical history and family history). Data on pharmacological treatment will be systematically collected from the medical records of the study patients using CRFs at baseline and at 6-month follow-up in both the intervention and control clinics.

Height and weight will be measured using the Seca 769 Digital Medical Scale stadiometer (Seca, Hamburg, Germany). Weight will be measured with the patient in light clothing, without shoes on the scale, and with a precision of 0.1 kg. Height will be measured to 0.1 cm using the stretch stature method of the stadiometer and then converted to metres. BMI will be calculated using the standard formula (weight in kg)/(height in metres)^2^.

WC will be measured to the nearest 0.1 cm using non-stretchable measuring tape with the patient standing in a relaxed position and arms at the side. The measurement will be taken at the midpoint between the lower rib margin (12th rib) and the top of the iliac crest in horizontal plane. Each measurement will be repeated twice. If the measurements are within 1 cm of one another, the average will be calculated. If the difference between the two measurements exceeds 1 cm, both measurements will be repeated.

Patients will be made to rest and will not be allowed to eat, drink caffeinated beverages, exercise, smoke cigarettes, or climb stairs for at least 15 min before BP measurements are taken. BP will be measured twice, 2 min apart, on the right arm in a sitting position, using an Omron IA2 model automatic digital blood pressure monitor (Omron Healthcare, Kyoto, Japan). Each patient will be seated upright with his/her right arm supported at the heart level. The mean of the first and second systolic and diastolic measurements will be reported as the BP value for individual patients if the difference is within 5 mmHg. If the readings differ by more than 5 mmHg, the measurements will be repeated.

### Administration of the questionnaires

Patients in both the intervention and control arms will be given a set of questionnaires to be self-administered, which include PAM-13-M, IPAQ-M, DEBQ-M, PACIC-M, SKIP-11 and a visual analogue scale to record the perceived absolute 10-year CVD risk.

Clear written and verbal instructions will be given on how to complete the questionnaires. Patients will be requested to circle or tick which options suit them the most. Patients will be encouraged to seek clarification from the investigators at any time, should any queries arise. They will also be reminded to answer the questionnaires themselves rather than getting help from their accompanying family members.

Patients will be given a pen to complete the questionnaires at a corner of the clinic equipped with tables and chairs. The investigators will ensure that patients do not interact with each other whilst answering the questionnaires. On average, patients will be expected to take approximately 30 min to complete the set of questionnaires. Once they have finished, they will hand the questionnaires to the investigators, who will then check the responses for completeness.

### Study tools

#### PAM-13-M questionnaire

The PAM-13 consists of 13 items measuring patients’ self-reported knowledge, skills and confidence for self-management [24]. It was developed in the English language using a Rasch model [24]. Each item has five response categories with scores ranging from 1 to 5: (1) ‘strongly disagree’, (2) ‘disagree’, (3) ‘agree’, (4) ‘strongly agree’ and (5) ‘not applicable’. The instrument design reflects the four stages of activation in a progressing degree of difficulty of the items: level 1 (patients believe that their role is important: items 1 and 2), level 2 (patients have confidence and knowledge to take action: items 3–8), level 3 (taking action: items 9–11) and level 4 (staying on course under stress: items 12 and 13). According to the PAM-13 scoring guidelines, the raw scores are transformed through natural logarithm to achieve a better expression of the relative distance between the scores. Then, items are transformed to a standardised metric ranging from 0 to 100 (0 = lowest activation; 100 = highest activation). The score is calculated by summing the raw scores and mapping the sum onto a scale of 0–100. A higher score of PAM-13 indicates a high level of patient activation [24]. The PAM-13 is one of the most extensively used, widely translated and tested instruments worldwide in measuring patient activation level in self-management. It has been translated into the Malay language and is currently being validated in the study population. Research licence to use this questionnaire will be obtained from Insignia Health, University of Oregon.

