### Sample size determination

Sample size is calculated using Power and Sample Size Calculation software version 3.1.2 [84], based on the findings of a randomised controlled trial evaluating the effects of a web-based self-management intervention for adults with chronic conditions on patient activation scores, measured by the PAM-13 questionnaire [48]. In the intervention group, the mean patient activation score at baseline was 65.33, and the mean score after the intervention was 71.30 (mean difference, 5.97 ± 9.70; t57 = 4.683; *P* < 0.001) [48]. In the control group, the mean patient activation score at baseline was 66.89, and the mean score at the end of the study period was 68.93 (mean difference, 2.04 ± 10.01; t67 = 1.677; *P* = 0.10) [48]. Therefore, the mean difference between the two groups was 3.93.

Based on this assumption, a sample size of 97 patients per group is sufficient to detect mean difference of δ = 3.93 in the patient activation score between the two groups, with a standard deviation of σ = 9.70 using a two-tailed *t* test of difference between means with 80% power (power = 0.8), 5% level of significance (α = 0.05), and sample size ratio of 1:1 between the two groups (m = 1). After considering a drop-out rate of 20%, the sample size required is 116 patients per group, giving a total of 232 patients to be recruited for this study.

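### The PAM-13-M scoring text gives 'not applicable' a score of 5, above 'strongly agree', and sums it, so each such answer raises that patient's activation score

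*Protocol article*

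**What the plan says.** All of the scoring text stands in the protocol article under Study tools, PAM-13-M questionnaire.

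- Length: "The PAM-13 consists of 13 items measuring patients’ self-reported knowledge, skills and confidence for self-management".
- Item scores: "Each item has five response categories with scores ranging from 1 to 5". The list of categories starts at 1 for strong disagreement and ends with "4) ‘strongly agree’ and (5) ‘not applicable".
- Total: "The score is calculated by summing the raw scores and mapping the sum onto a scale of 0–100".
- Direction: "A higher score of PAM-13 indicates a high level of patient activation". The same section labels 0 as the lowest activation and 100 as the highest.
- Outside source: "According to the PAM-13 scoring guidelines, the raw scores are transformed through natural logarithm". The guidelines are cited here for the transformation and the 0 to 100 metric. The section does not report what they say about 'not applicable'.

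The Primary outcome section rests on this score: "The primary outcome will be measured by the mean change in patient activation score". The Effectiveness analysis section compares mean changes within and between the two arms, from baseline to 6 months.

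**The concern.** Categories 1 to 4 form an ordered agreement scale. Category 5 lies off that scale, because it says only that the item does not fit the patient. The text nevertheless calls all five numbers scores, sums the raw scores and reads a higher total as more activation. Nothing in the section leaves category 5 out of the sum.

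The article is not silent on scoring here. It states a rule, and that rule ranks an inapplicable item above full agreement. The described data checks would not catch it: under Administration of the questionnaires and Data management, forms are checked for completeness and patients are telephoned about missing data. A ticked 'not applicable' is a complete answer with a permitted code of 5.

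At stake is the meaning of the primary endpoint. If use of the option changed during the trial, a patient who moved from 'not applicable' to 'agree' would lose points. A patient who moved the other way would gain points without being more activated.

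**Working it through.** **Inputs.** From the PAM-13-M section: 13 items, scores 1 to 5, 'strongly agree' = 4, 'not applicable' = 5, sum mapped to 0–100. From Sample size determination: difference 3.93, SD 9.70, 80% power, two-sided 5% level, 1:1 allocation.

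**Assumption.** The conversion table is not in the article, so I use a linear map, score = 100 × (raw − 13)/(max − 13). I take max = 52 (four scored categories) and max = 65 (five, as literally stated). The real conversion is described as logarithmic, so the point values are indicative. The ordering is not affected: any increasing map places a higher sum above a lower one.

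**1. The plan's own figure.** The protocol states that "a sample size of 97 patients per group is sufficient to detect mean difference of δ = 3.93 in the patient activation score". The difference is 5.97 − 2.04 = 3.93. By the normal approximation, n = 2 × (1.960 + 0.842)² × 9.70²/3.93² ≈ 95.6, so 96 per group. The t-based calculation gives 96.6, so 97. The figure reproduces, and 3.93 is the yardstick below.

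**2. Ends of the scale.**
- 'Strongly agree' to every item: 13 × 4 = 52.
- 'Not applicable' to every item: 13 × 5 = 65.
- With max = 65, the first patient scores 100 × 39/52 = 75 and the second 100.
- With max = 52, the first scores 100 and the second 100 × 52/39 = 133.3, outside the stated range.

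On neither map does the summing rule agree with the section's own 0–100 scale and its label for 100.

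**3. One 'not applicable' answer, one patient.**

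| Answer replaced | Raw points added | Max = 65 | Max = 52 |
|---|---|---|---|
| disagree (2) | 3 | 300/52 = 5.8 | 300/39 = 7.7 |
| agree (3) | 2 | 200/52 = 3.8 | 200/39 = 5.1 |
| strongly agree (4) | 1 | 100/52 = 1.9 | 100/39 = 2.6 |

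**4. From one patient to the treatment effect.** Let D be the between-arm difference in the mean change, baseline to 6 months, in the number of 'not applicable' answers per patient. The bias is about D × the shift per item.
- If use is stable, or changes equally in both arms, D = 0 and the error largely cancels.
- For 'agree' as the alternative answer, the bias reaches 3.93 when D = 3.93/5.13 = 0.77 (max = 52) or 3.93/3.85 = 1.02 (max = 65).
- If one patient in ten in one arm changed by one item in the same direction and the other arm did not change, D = 0.1 and the bias is about 0.4 to 0.5 points.

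**5. With 'not applicable' treated as missing.** Take 12 'agree' answers and one 'not applicable'. The stated rule gives 12 × 3 + 5 = 41, or 71.8 on the 13–52 map. Rescaling the answered items gives (36/12) × 13 = 39, or 66.7, the same as for 13 'agree' answers.

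**The case against.** The strongest reply is that the section does not rest on the summing sentence alone. It describes a Rasch-based instrument, refers to the PAM-13 scoring guidelines and says that a research licence will be obtained. The numbers 1 to 5 may be response codes loosely called scores, and the licensed scoring may already leave 'not applicable' out. That the literal rule can run past 100 on a four-category map makes a misdescription plausible. This stands as a limit on what can be concluded: the article does not show how the data will actually be scored. It does not rescue the text, because the guidelines are cited only for the transformation and the metric.

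A reader might also infer that the primary outcome, and so the treatment effect, is inflated. The documents do not support that. What is raised is the score of a patient who uses the option. The outcome is a change compared between arms, so bias needs use of the option to change differently by arm, and it could go either way. If coaching with the app made more items applicable, the effect would be understated. The article gives no frequency of use. All participants have had at least two follow-up visits for metabolic syndrome in the past year and may ask investigators for clarification, so heavy use is not evident.

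Nor should the one-item shift of 3.8 to 5.1 points be set directly against 3.93 as though a single answer could produce the trial's effect. The first is one patient's shift and the second is a difference between group means; step 4 of the working gives the fair comparison.

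The remaining reply is that an article may leave unscored responses to a manual or analysis plan. That would answer an omission, but here a rule is stated, and it is wrong as stated.

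**Conclusion.** The point holds as a wrong stated rule for the primary outcome. As written, 'not applicable' counts above 'strongly agree', and the top of the scale need not mean the highest activation. That ordering follows from the text under any increasing conversion.

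The sizes rest on an assumed linear map: about 3.8 to 5.1 points per item for one patient when 'agree' is the alternative answer. The treatment effect would be displaced by the full planned 3.93 only if the arms differed by about 0.8 to 1.0 items per patient in the change. Bias in the trial result is therefore possible but not shown, and its direction is open. Whether the data will be mis-scored or the scoring is merely misdescribed cannot be settled from the article. The text needs correcting in either case, before any questionnaire is scored.

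**What to change.** State in the PAM-13-M section that only responses 1 to 4 are scored and that 'not applicable' is treated as missing. Take the raw score over the answered items and rescale it to 13 items before conversion to 0–100. Prespecify a minimum number of answered items below which the score is missing, and apply the same rule at baseline and 6 months. Check the wording against the scoring guidelines the trial will use, so that text and scoring syntax agree. Reporting the number of 'not applicable' answers by arm and visit would show whether use of the option shifted.

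The cost is a few sentences of protocol text and the matching scoring syntax; data collection does not change. The downside is that patients with many 'not applicable' answers will have a missing primary outcome score.

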#### IPAQ-M

The IPAQ was developed to measure health-related PA in the English language [78] and was previously translated into the Malay language and validated in the Malaysian population [70]. The IPAQ-M short version comprises of 12 items, covering vigorous, moderate, walking, sitting and sleeping activities [70]. Patients are required to report the activities performed during the last 7 days and to include only activities that lasted 10 min or more per session. IPAQ will be scored according to its scoring protocol [79]. Continuous score will be expressed as metabolic equivalent task (MET) minutes per week: MET level × minutes of activity/day × days per week [79]. The scores will then be categorised into ‘low’, ‘moderate’ and ‘vigorous’ PA levels in accordance with the Malaysian CPG on Primary and Secondary Prevention of Cardiovascular Disease 2017 [64]. The IPAQ-M short version has acceptable validity for moderate, vigorous and total PA and was found to be reliable for assessing PA of Malay adults [70].

#### DEBQ-M

The DEBQ was developed in the English language [80] and has been translated into the Malay language and validated in the Malaysian population [71]. The DEBQ-M contains 33 items to measure emotional, external and restrained eating behaviours. Emotional eating is assessed by 13 items, whereas external and restrained eating behaviours are assessed by 10 items each. The questions that assess the three different behaviours appear in random order in the questionnaire and are answered according to a Likert scale with a scoring system identified as follows: 1 = never, 2 = rarely, 3 = sometimes, 4 = often, and 5 = very often. There are three subscales in the instrument. For each subscale, the score is added and divided by the number of items in the subscale to obtain the average score for emotional, external and restrained eating for a person [71].

#### PACIC-M questionnaire

The PACIC questionnaire consists of a 20-item patient self-report instrument developed in the English language to assess the extent to which patients with chronic disease receive care that aligns with the CCM [81]. It has recently been translated into the Malay language and cross-culturally adapted and validated to produce the PACIC-M [72]. It measures care that is patient-centred, proactive and planned, which includes collaborative goal setting, problem-solving and follow-up support [81]. Each item is scored on a 5-point Likert scale, with 1 being ‘no’ or ‘never’ and 5 being ‘yes’ or ‘always’. The higher the score, the more aligned is the perceived care to CCM. PACIC-M was found to be highly reliable (Cronbach’s α of 0.94 with mean interitem correlation of 0.45) and valid to be used in assessing three CCM model domains [72].

#### SKIP-11 questionnaire

SKIP-11 is the translated and validated Malay version [73] of the Medical Interview Satisfaction Scale [82]. SKIP-11 is used to measure patient–physician interaction satisfaction and consists of 11 questions representing three subdomains of patient–physician interaction satisfaction. There are four questions pertaining to information provision (‘Distress relief’ subdomain), four questions regarding the physician’s communication skills (‘Rapport’ subdomain) and three questions assessing the adherence intent as an outcome of the overall interaction experience (‘Interaction outcome’ subdomain). All 11 items are scored using a 5-point Likert scale whereby for positively worded items, a score of 5 is for ‘strongly agree’ and a score of 1 is for ‘strongly disagree’. For the negatively worded items, score 1 is for ‘strongly agree’ and score ‘5’ is for strongly disagree. Each response will be added together to give a total score within the range of 11 (minimum) and 55 (maximum). Total score for each subdomain is also calculated and analysed, where the minimum and maximum scores are determined by the number of items present in each subdomain. The levels of satisfaction will be determined by the proximity of the score to either the minimum or maximum score for each subdomain. The closer proximity of the score to the maximum score will reflect good satisfaction level and vice versa [73].

#### Accuracy of the perceived absolute 10-year CVD risk

The perceived absolute 10-year risk of heart attack and stroke will be estimated separately by the patients along a visual analogue scale [74]. The average of these values will be taken as the perceived absolute 10-year CVD risk for the patients. The patients’ actual absolute 10-year CVD risk will be calculated using the FRS general CVD risk prediction chart [75, 76], which has been validated in the Malaysian population [83]. The accuracy of the CVD risk perception will be defined as the absolute difference between the perceived and actual risk, which will be inversely related (i.e., the lower the absolute difference, the more accurate the patients’ CVD risk perception) [74].

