### Exclusion criteria

Patients who fulfil any of the following criteria will be excluded:
Type 1 diabetes mellitusReceiving renal dialysisPresent with severe hypertension (systolic BP > 180 mmHg and/or diastolic BP > 110 mmHg) at recruitmentDiagnosed with conditions resulting in secondary hypertensionDiagnosed with circulatory disorders requiring referral to secondary care over the last 1 year and during the course of the study (e.g., unstable angina, heart attack, stroke, transient ischaemic attacks, peripheral vascular diseases)Receiving shared care at primary and secondary care centres for CVD (coronary artery diseases, stroke, transient ischaemic attacks, peripheral vascular diseases)Receiving chemotherapy/radiotherapy or palliative careDiagnosed with a psychiatric illness such as schizophrenia, bipolar disorder, major depressionDiagnosed with cognitive impairment such as dementiaPregnantEnrolled in another intervention study

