## Discussion

To the best of our knowledge, the EMPOWER-SUSTAIN project is the first self-management e-health intervention designed for patients with MetS in the Malaysian primary care setting. The pilot randomised controlled trial will be conducted to evaluate the feasibility and potential effectiveness of the EMPOWER-SUSTAIN intervention, including recruitment rate, methods of randomisation, retention rate, selection of primary and secondary outcome measures, sample size calculation, whether the intervention could be delivered as intended, and methods of statistical analysis to evaluate the potential effectiveness [44, 45]. All of these aspects will be useful for further exploration in a larger definitive trial.

The EMPOWER-SUSTAIN Self-Management e-Health Intervention is expected to yield important new evidence on the potential improvements of patient activation and self-management behaviours among patients with MetS in a developing country. It is hypothesised that patients’ activation, WC, BMI, blood pressure, PA level, eating behaviour, perception and experience of receiving chronic disease care, patient–physician satisfaction, and perceived absolute 10-year CVD risk would improve with the EMPOWER-SUSTAIN Self-Management e-Health Intervention.

The EMPOWER-SUSTAIN intervention is a complex, multifaceted chronic disease management strategy based on three CCM elements (i.e., delivery system design, self-management support and decision support). It consists of training the PCPs, nurse, and patients to use the EMPOWER-SUSTAIN web-based self-management mobile app, strengthening patient–physician relationship, and reinforcing the use of relevant CPG for management and prescribing. This intervention is developed on the basis of MRC recommendations, guided by the best available evidence and appropriate framework [46, 47].

It is well established that the CCM is one of the best-known models to transform chronic disease care [11]. The EMPOWER-SUSTAIN intervention focuses on linking informed, activated patients with proactive and prepared practice team (i.e., PCPs and nurse) [11, 86]. The self-management mobile app is developed as a tool for health care providers to support and engage patients so that they are empowered with knowledge, skills and confidence to take independent actions to manage their own health [11, 12].

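### Perceived CVD risk is the average of two component risks but is compared with a composite risk, so a patient who judges both unequal risks correctly is scored as inaccurate (secondary outcome)

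*Protocol article*

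**What the plan says.** All of the rule is in the protocol article, in the section on accuracy of the perceived absolute 10-year CVD risk.

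- Elicitation: "The perceived absolute 10-year risk of heart attack and stroke will be estimated separately by the patients along a visual analogue scale".
- Combination: "The average of these values will be taken as the perceived absolute 10-year CVD risk for the patients".
- Comparator: "The patients’ actual absolute 10-year CVD risk will be calculated using the FRS general CVD risk prediction chart".
- Score: "The accuracy of the CVD risk perception will be defined as the absolute difference between the perceived and actual risk". The section adds that a smaller difference means a more accurate perception.

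The Secondary outcomes list makes the change in this quantity an outcome: "Change in accuracy of CVD risk perception will be measured by the absolute difference between the perceived absolute 10-year CV risk and the actual calculated" risk from the Framingham chart. The Hypotheses section also speaks of accuracy.

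Three other places name perceived risk itself: the Methods paragraph of the abstract, the Effectiveness analysis section, and the Discussion, which expects that "perceived absolute 10-year CVD risk would improve".

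**The concern.** The two sides of the subtraction are different quantities. One is the mean of two single-event risks. The other is the risk of having any event from a group that contains both. The mean of two correct answers is in general not the correct composite answer, and the discrepancy always has the same sign: it makes correct patients look like underestimators.

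Because the score is an absolute difference and the outcome is its change, the offset does not simply subtract out. A patient who starts by overstating both risks may begin near zero error and move away from zero on becoming correct. The outcome could then misstate whether perception got better or worse. Judging whether the outcome measures are appropriate is one of the stated purposes of the pilot, so a mis-scaled measure could be carried into the definitive trial.

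**Working it through.** The plan states no figure on this point, so there is none to reproduce. The check is probability bounds plus illustrations.

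**Inputs from the article.** p1 = perceived heart-attack risk, p2 = perceived stroke risk, m = (p1 + p2)/2, F = Framingham general CVD risk, score = |m − F|.

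**Inputs assumed.** The component risks below. The article gives none and says nothing about how far the two events overlap.

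**Step 1: what the composite can be.** The risk of at least one of the two events satisfies

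max(p1, p2) ≤ P(either) ≤ min(1, p1 + p2),

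and equals 1 − (1 − p1)(1 − p2) under independence. The mean never exceeds max(p1, p2) and is strictly below it when p1 ≠ p2. So with unequal answers, m lies below every value that a coherent either-event risk can take.

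**Step 2: does general CVD contain both events?** The article does not list the events in the Framingham endpoint. Its own use of the term, in the Exclusion criteria, is broad: "CVD (coronary artery diseases, stroke, transient ischaemic attacks, peripheral vascular diseases". The argument needs only that heart attack and stroke are included. Any further events raise F and widen the gap.

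**Step 3: score for a patient who is exactly right on both**, taking F as the either-event risk:

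| True p1, p2 (assumed) | Average | Either event: bounds | Independent | Scored error: bounds | Independent |
|---|---|---|---|---|---|
| 12%, 4% | 8% | 12–16% | 1 − 0.88 × 0.96 = 15.52% | 4–8 points | 7.52 |
| 10%, 10% | 10% | 10–20% | 1 − 0.90 × 0.90 = 19% | 0–10 points | 9 |
| 20%, 10% | 15% | 20–30% | 1 − 0.80 × 0.90 = 28% | 5–15 points | 13 |

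The error is zero only if the two risks are equal, the events coincide fully, and the composite contains nothing else.

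**Step 4: who is scored as perfect?** Under independence, it is a patient whose average equals F. Relative to the truth, both answers must be inflated by F/m: 15.52/8 = 1.94, 19/10 = 1.90 and 28/15 = 1.87 in the three rows.

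**Step 5: direction of change.** True risks 12% and 4%, independent, F = 15.52%.

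- Baseline answers 22% and 8%: average 15%, error 0.52.
- Six-month answers 12% and 4% (now correct): average 8%, error 7.52.
- Scored change: 7.52 − 0.52 = 7.0 points worse, for a patient who became right.

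**Step 6: the same patient with the two answers combined as a union.**

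- Baseline: 1 − 0.78 × 0.92 = 28.24%, error 12.72.
- Six months: 15.52%, error 0.
- Scored change: 12.72 points better, which is the right direction.

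**The case against.** **The rule follows a published method.** The section cites a source for the two-scale elicitation and for the absolute-difference definition. The averaging sentence carries no citation of its own, and the article gives no reason for averaging. Comparability with earlier work is a fair reason to keep reporting the average. It does not put a mean and a composite on the same scale.

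**The sizes are assumed, and independence puts them near the top of their ranges.** This stands. At 10% and 10% the lower bound of the error is zero, so the defect is certain only when the two risks differ. The actual size in this population is unknown.

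**The replacement formula is imperfect.** This also stands. Independence is an assumption, and a gap remains if the Framingham endpoint counts other events. A patient who has been told an overall risk of 10% and marks 10% on both scales would be scored as holding 19%. The max(p1, p2) bound returns 10% for that patient, which is one reason to report the bounds.

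**The same rule applies in both arms and at both visits.** True: if the intervention does not change the answers, the rule by itself creates no arm difference. The measure exists to detect changed answers, however, and Step 5 shows that a change can be scored with the wrong sign.

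**The wording differences are shorthand.** Largely so. The Hypotheses, the Secondary outcomes list and the definition all say accuracy, and the definition fixes which direction is better. This is a matter of tidying.

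**A stronger reading that the documents do not support.** A reader might infer that the app shows intervention patients their overall CVD figure, that they repeat it on both scales, and that any arm difference would be recall of a displayed number. The article gives only the title of an app section on cardiovascular risks. It does not say that a 10-year percentage is displayed. Controls receive the programme's booklet on global cardiovascular risks, and that booklet's content was considered for the app. Differential exposure to a displayed figure is not established.

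**Conclusion.** The concern holds for this one secondary outcome. The article explicitly averages two component risks and compares the result with a composite, and no other section repairs the mismatch. Whenever the two risks differ, a patient correct on both is scored as inaccurate, always in the direction of underestimation. That conclusion rests only on general CVD including heart attack and stroke.

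The size rests on assumed component risks: 4 to 8 points at 12% and 4%, 0 to 10 at 10% and 10%, and 5 to 15 at 20% and 10%. The independence values are 7.5, 9 and 13. These are illustrations, not estimates for this trial. The documents do not show that the rule will bias the comparison between arms by any particular amount, or that an arm difference would reflect recall. The primary outcome (PAM-13-M) and the sample size do not depend on it.

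**What to change.** 1. Derive perceived composite risk from the two recorded answers as 1 − (1 − p1)(1 − p2), and take its absolute difference from the Framingham general CVD risk as the accuracy outcome.
2. Repeat the analysis with max(p1, p2) and with min(1, p1 + p2) as sensitivity bounds.
3. Report the plain average as a further sensitivity analysis, for comparability with the cited method.
4. State that the main formula assumes independence, and that a residual gap remains if the Framingham endpoint includes events beyond heart attack and stroke.
5. In the abstract, the Effectiveness analysis section and the Discussion, name the outcome as accuracy (the absolute difference), to match the Hypotheses, the Secondary outcomes list and the definition.

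The cost is a derived-variable formula, three sensitivity analyses and some wording. No new data are needed, because both answers are already collected. The price is less direct comparability of the main result with earlier work, which item 3 covers.
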